#### Secondary analyses

Secondary analyses with be comparison of quality of life and health status, and incremental cost per quality-adjusted life-year with confidence interval by Fieller’s theorem [45, 46]. In analysis of quality of life, missing data will be addressed by imputation with sensitivity analysis.

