## Methods/Design

### Aims and objectives

This is a three-arm, randomized controlled trial that compares usual care (no PHF) to two patient-held PHFs: an e-PHF carried on a USB flash drive, and a p-PHF, in patients that are 60 years or older and who have two or more chronic medical conditions (see Inclusion criteria). The primary objective is to determine whether use of a PHF compared to usual care, over 48 months, reduces a combined endpoint of deaths, overnight hospitalizations and serious out-of-hospital events.

The secondary objectives are to determine whether use of a PHF over 48 months compared to usual care improves quality of life as measured by the EQ-5D [34, 35], and health status as measured by the Short-Form Health Survey SF-36 [36], and whether PHFs are acceptable in terms of user-friendliness, convenience and usefulness to patients and their health-care providers.

Additional objectives are to determine whether use of a PHF over four years compared to usual care improves delivery, quality and efficiency of health care by improved health literacy, reduction in medication errors, reduction in duplicative investigations, improved adherence to management plans, reduced health-care utilization and reduced costs.

The assigned intervention (e-PHF, p-PHF or no PHF) will be used for 48 months. Patients will also be followed up on for an additional 36 months beyond the conclusion of the randomized trial. This protocol is reported in accord with the Standard Protocol Items: Recommendations for Interventional Trials (SPIRIT) 2013 guidance for protocols in clinical trials [37].

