#### Hypotheses

The primary hypothesis is that addition of a patient-held PHF to usual care results in fewer important clinical events using a combined endpoint of deaths, overnight hospitalizations and serious out-of-hospital events compared to usual care. The secondary hypothesis is that addition of a patient-held PHF to usual care improves quality of life and health status.

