#### Primary statistical analyses

There are two co-primary analyses because this is a three-arm, randomized controlled trial: e-PHF versus usual care and p-PHF versus usual care. Both analyses use the combined endpoint of deaths, hospitalizations (excluding day-only admissions) and adjudicated serious out-of-hospital events, and both use an adaptation of the Andersen-Gill formulation [43] of the proportional hazards model in order to capture possibly correlated events in the same subject. A robust variance estimate [44] will be used that takes into account the possibility of correlation of risk of multiple events within a subject by including an additional time-dependent covariate indicating whether the event was the first or subsequent event of its kind. The level of significance for each analysis is 0.025. This is an intention-to-treat analysis.

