#### Additional analyses

9.Health service utilization and health-care costs;10.Medication errors, duplicative investigations;11.Clinical workflow;12.Management plans uptake and documentation;13.Health literacy;14.Information technology and computer expertise and15.Adverse events.

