There is considerable evidence that patients like the PHF, believe it is useful and feel more in control of their care when they have access to it. These are important outcomes. The fundamental question is whether use of a PHF is acceptable enough short term to enable demonstration translation into important patient outcomes. It may well be that in the near term, physician visits and even hospitalizations may increase due to attention to aspects of chronic diseases previously overlooked. One mechanism by which we believe access to a PHF will result in changes to patient outcomes and processes involves the use of multiple medications among an older patient population with complex health problems. However, the important question is whether a PHF and any accompanying increase in intensity of care will translate into later benefits in morbidity, as measured by significant hospitalizations, which is probably the most feasible overall capture of morbidity. Only with a properly designed trial using randomization can one obtain a valid demonstration of a reduction in morbidity and in mortality. However, to date this has not been easy to demonstrate, and successful demonstration may vary with exactly what benefit is being considered and, as importantly, what time course is being used. Our proposal addresses both trial duration and size in a randomized setting with important clinical outcomes.

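### The only joint cost–QALY measure named is a ratio with a Fieller interval, which hides the direction of effect and is usually unbounded when the QALY difference is small; net monetary benefit should be the secondary economic result

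*Protocol article*

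**What the plan says.** Under Secondary analyses the protocol article lists "Secondary analyses with be comparison of quality of life and health status", followed by "incremental cost per quality-adjusted life-year with confidence interval by" Fieller's theorem. It gives no confidence level for that interval, no willingness-to-pay value and no other joint measure. The only level in the analysis section belongs to the co-primary tests: "The level of significance for each analysis is 0.025". The comparisons are "e-PHF versus usual care and p-PHF versus usual care".

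Three other places bear on the likely sign of the ratio:
- Hypotheses: the secondary hypothesis is that "addition of a patient-held PHF to usual care improves quality of life and health status".
- Aims and objectives: the additional objectives include "improved adherence to management plans, reduced health-care utilization and reduced costs".
- Discussion: "It may well be that in the near term, physician visits and even hospitalizations may increase". It also accepts that greater attention to health in the PHF arms could move the hospitalization rate up or down.

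Costs are analysed on their own as well, under Additional analyses: "Health service utilization and health-care costs".

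**The concern.** A cost-per-QALY ratio is easy to read when the intervention costs more and gives more health. This protocol aims at a different quadrant, better quality of life at lower cost, where the ratio is negative. A negative ratio also arises when the PHF costs more and lowers quality of life, and the Discussion does not rule out a rise in use of care. The ratio and its interval do not tell these two results apart. Even when the quadrant is known, the size of a negative ratio does not rank results.

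The Fieller interval adds a second difficulty. It is finite only if the QALY difference is itself statistically significant. With a small QALY effect, the reported result would usually be two disjoint rays or the whole line. At stake is how readable the trial's one named joint economic result will be, although the EQ-5D and utilization data for a clearer one are collected throughout (Table 1).

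**Working it through.** **Inputs from the protocol.** The sample-size section gives 158 per arm for analysis and 264 per arm (792 in all) after a 40 % dropout allowance. These figures reproduce. Taking 0.70 against 0.525 (a 25 % reduction), two-sided 0.025, 80 % power and a continuity correction gives 158, and the exact power of Fisher's test at 158 is 80.3 %. Then 158/0.6 = 263.3, rounded up to 264, and 3 × 264 = 792. The protocol gives no figure for the economic analysis.

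**Assumptions.** The protocol states no QALY SD, QALY gain, cost SE, willingness-to-pay value or confidence level. For illustration: SD of 48-month QALYs 0.6 to 1.0, true gain 0 to 0.20, 95 % interval (97.5 % as the alternative).

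**Step 1: the Fieller set.** Let dC and dE be the cost and QALY differences. The set holds every R with (dC − R·dE)² ≤ z²·[Var(dC) − 2R·Cov + R²·Var(dE)]. Write A = dE² − z²·Var(dE), B = dE·dC − z²·Cov and C = dC² − z²·Var(dC). If A > 0, the limits are (B ± √(B² − AC))/A. If A ≤ 0, the set is unbounded. Reversing the signs of both dC and dE changes none of A, B and C.

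**Step 2: dominant against dominated.** Assume SEs of 0.06 QALY and 1,500 in cost, with no covariance.
- dE = +0.2, dC = −5,000: ratio −25,000; A = 0.04 − 3.8415 × 0.0036 = 0.02617; interval −67,108 to −9,313.
- dE = −0.2, dC = +5,000: ratio −25,000; same interval.
- Net monetary benefit, λ·dE − dC, at an assumed λ of 50,000: +15,000 and −15,000. Its SE is √(50,000² × 0.0036 + 1,500²) = 3,354, so the 95 % intervals are +8,426 to +21,574 and −21,574 to −8,426.

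**Step 3: ordering within the hoped-for quadrant.**

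| dE | dC | Ratio | Net benefit at λ = 50,000 |
|---|---|---|---|
| +0.1 | −2,000 | −20,000 | 7,000 |
| +0.2 | −2,000 | −10,000 | 12,000 |
| +0.2 | −4,000 | −20,000 | 14,000 |

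Doubling the health gain halves the size of the ratio. Doubling both benefits leaves it unchanged. Net benefit ranks the three as expected.

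**Step 4: how often the set is unbounded.** The probability is Φ(z − d/SE) − Φ(−z − d/SE), where d is the true QALY difference and SE = SD·√(2/n). For n = 264, SD 0.8 and d = 0.10: SE = 0.0696 and d/SE = 1.436, so Φ(0.524) − Φ(−3.396) = 0.70. For a 95 % interval:

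| True QALY difference | 264 per arm, SD 0.6 / 0.8 / 1.0 | 158 per arm, SD 0.6 / 0.8 / 1.0 |
|---|---|---|
| 0 | 95 / 95 / 95 % | 95 / 95 / 95 % |
| 0.05 | 84 / 89 / 91 % | 89 / 91 / 93 % |
| 0.10 | 52 / 70 / 79 % | 68 / 80 / 86 % |
| 0.20 | 3 / 18 / 37 % | 16 / 40 / 57 % |

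Free of any SD assumption, the figure is 83 % at a true difference of 1 SE, 48 % at 2 SE and 20 % at 2.8 SE. With a 97.5 % interval these become 89, 60 and 29 %, and the null figure becomes 97.5 %. Simulation (400,000 trials per setting) agreed with the formula.

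**The case against.** The strongest reply has five parts.

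- *The quadrant is known.* The cost and QALY differences must be computed to form the ratio, and quality of life and costs are also analysed separately. An analyst would not in practice confuse dominant with dominated. This stands, but it does not solve the ordering problem in Step 3, and two separate margins do not express joint uncertainty.
- *An unbounded set is valid.* This stands. The Fieller set is exactly the set of λ at which the net-benefit interval includes zero, so net benefit adds no evidence. The set can still exclude some thresholds. With a true QALY difference of zero and a true cost difference of 2 SE, the simulations gave the whole line in 38 % of trials and two rays in the other 57 %. What net benefit adds is direction, order and a bounded interval at every threshold.
- *Cost reduction is not a hypothesis.* Correct: it is an additional objective. A negative ratio is therefore hoped for, not formally predicted.
- *The figures between the extremes are assumed.* Correct. The 158-per-arm column is also pessimistic, because all randomized subjects are analysed, missing quality-of-life data are imputed, and measures after discontinuation are sought.
- *A condensed article may leave net benefit or acceptability curves to a fuller plan.* It may, and their absence here is not an error. The point concerns the measure and interval method that the article does fix.

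**Conclusion.** The point holds as a worthwhile improvement to a secondary analysis, not as an error of method. The only named joint measure gives the same ratio and interval for opposite results, cannot be ranked in the quadrant the trial hopes for, and is unbounded in most trials when the QALY effect is small. The null figure of 95 % depends only on an assumed 95 % level. The 52 to 79 % at 0.10 QALY also depends on assumed SDs of 0.6 to 1.0 and 264 per arm.

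A reader might go further and infer that value for money will be judged from this ratio alone, or that the ratio cannot discriminate at all. The documents do not support either. The protocol states no such decision rule and analyses quality of life and costs separately. With a clear QALY difference the interval is usually finite: at 0.20 QALY and 264 per arm it is unbounded in only 3 to 37 % of trials. The primary analysis and sample size are untouched.

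**What to change.** For each PHF arm against usual care, make incremental net monetary benefit, λ × (QALY difference) − (cost difference), the secondary economic result. Give its confidence interval, at a stated level, over a stated range of willingness-to-pay values, or use an acceptability curve. Always report the cost and QALY differences beside it. Keep the ratio and its Fieller set as a supplementary result, state the quadrant, and report them whatever they turn out to be. A rule that shows them only when they are positive and finite would make reporting depend on the result.

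The cost is a change of wording and a few lines of code on data already being collected. The downside is that the result appears over a range of thresholds and not as one figure.

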#### Other analyses (exploratory)

Analyses as for the primary analysis but adjusted for study completion after 48 months of treatment (completers analysis);Analyses as for the primary analysis but adjusted for study completion after 48 months of treatment and adherence with interventions (compliers analysis);Subgroup analysis of each of the composite endpoints: hospitalizations, serious out-of-hospital events and deaths;Subgroup analysis of day-only hospitalizations;Analysis of patient acceptability;Analysis of health-care provider acceptability;Qualitative exit interviews andSubgroup analyses of primary and secondary endpoints adjusted by covariates: age, health literacy, comorbidity status and computer and information technology literacy.

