### Methods: statistical analysis plan

All analyses will include all subjects randomized regardless of whether or when they may have withdrawn from the study. Therefore, for the primary and secondary objectives, the analysis will follow intention-to-treat principles. However, a completer’s analysis which is a comparison based on random allocation of subjects with complete data at the end of the trial, will also be undertaken as well as an as-treated complier’s analysis, which is based on the actual intervention and for how long it was utilized. The completer’s analysis and the as-treated analyses are exploratory analyses only.

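### The exploratory completers and compliers analyses use a composite that includes death, yet condition on completion, adherence and duration of use, which death itself cuts short.

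*Protocol article*

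**What the plan says.** The protocol article describes these analyses in two places.

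- **Methods: statistical analysis plan.** The governing rule is "All analyses will include all subjects randomized regardless of whether or when they may have withdrawn from the study". As exceptions, the completers analysis is a "comparison based on random allocation of subjects with complete data at the end of the trial", and the compliers analysis is as-treated, "which is based on the actual intervention and for how long it was utilized". The section adds that the completers analysis and "the as-treated analyses are exploratory analyses only".
- **Other analyses (exploratory).** Here both are run like the primary analysis. The first is "adjusted for study completion after 48 months of treatment (completers analysis") and the second reads "Analyses as for the primary analysis but adjusted for study completion after 48 months of treatment and adherence with interventions (compliers analysis").

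The endpoint carried over is set under Primary statistical analyses: "Both analyses use the combined endpoint of deaths, hospitalizations (excluding day-only admissions) and adjudicated serious out-of-hospital events". The Discussion states that hospitalizations and deaths will be captured whether or not a patient has withdrawn.

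**The concern.** Completion of 48 months, adherence and duration of use all arise after randomization. Death is a component of the endpoint, and it also ends participation and ends use of the portable health file (PHF). Selecting on these variables, or adjusting for them, therefore selects on or adjusts for part of the outcome, and the arms are no longer compared as randomized.

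The sample size allows for up to 40 % discontinuation, and the Discussion says the design depends on compliance by patients and providers. These two analyses are where a reader would look for the effect in people who used the PHF. A distorted estimate there could be read as support for, or against, a benefit in users.

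**Working it through.** **1. Deaths at stake.** Inputs are from the Discussion: annual mortality of 0.95 % and 1.68 % for women and 1.72 % and 2.90 % for men, in two equal age groups.
- Mean annual rate: (0.95 + 1.68 + 1.72 + 2.90) / 4 = 1.8125 %. Over four years: 4 x 1.8125 = 7.25 %, which reproduces the stated figure.
- Per arm of 264: 264 x 0.0725 = 19.1 deaths.
- The rate is for ages 65 to 74 in the general population. The trial enrols multimorbid patients from age 60 with no upper limit, so higher mortality is plausible.

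**2. The readings that the text allows.**

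| Reading | Source | What happens to early deaths |
|---|---|---|
| Restrict to those who finish 48 months | one reading of complete data at the end of the trial | About 19 subjects per arm leave, with their deaths and earlier hospitalizations |
| Completion as a covariate | the adjusted wording under Other analyses | All stay in the model, but every death before 48 months is in the non-completer stratum |
| As-treated by total duration of use | Methods: statistical analysis plan | A subject who dies at month 12 has at most 12 months of use; anyone classed with longer use survived beyond that by definition (immortal time) |

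Each conditions on something that death determines.

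**3. Illustrative size.** The simulations assume a gamma-distributed subject effect with variance 1, shared by death and hospitalization. None of the simulation assumptions is in the protocol. They give about 69 to 71 % of control subjects with any event, against the protocol's planning value of at least 70 %.

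*Both arms restricted to survivors* (0.55 hospitalizations per year in control):

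| True effect | Mortality | Ratio, all subjects | Ratio, survivors |
|---|---|---|---|
| None | about 7 % | 1.00 | 1.00 |
| Hospitalization and death both reduced 25 % | about 7 % | 0.756 | 0.763 |
| Same | about 18 % | 0.766 | 0.785 |
| Death only reduced 25 % | about 7 % | 1.00 | 1.02 |
| Same | about 18 % | 1.00 | 1.05 |

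*No effect, hospitalizations only, sicker subjects more likely to drop out.* The completer ratio is 1.00 with 40 % dropout in both arms, 0.89 with 40 % in the PHF arm and 20 % in usual care, and 0.84 with 40 % and 10 %. With the arms exchanged these become 1/0.89 = 1.12 and 1/0.84 = 1.19.

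*No effect, PHF completers against all usual care* (control mean 2.33 hospitalizations per 48 months, 40 % discontinuation unrelated to outcome). The ratio is 0.93 at 7.25 % mortality and 0.87 at 14 %. With the variance between 0.5 and 2, the ranges are 0.95 to 0.90 and 0.90 to 0.80. Subjects who die carry about 10 % and 20 % of all events. If death before discontinuation counts as completed follow-up, the ratio at 7.25 % mortality is about 1.02.

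**The case against.** The strongest case against has five parts.

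- **Exploratory status.** Both analyses are labelled exploratory, and the co-primary analyses are intention-to-treat with outcomes captured after withdrawal. This stands: the trial's main conclusion is untouched.
- **Whether deaths are dropped.** A reader might infer that these analyses necessarily discard every death. The document does not support that. Adjusting is not restricting, and a subject followed until death could be held to have complete data. Exclusion is one reading among several. The other readings still condition on a consequence of the outcome.
- **Whether a false benefit follows.** A reader might infer that the analyses favour the PHF when it does nothing. The document does not support that either. The ratio of 0.93 needs PHF completers set against unfiltered usual care, and nothing in the text limits the completion condition to the PHF arms. Filtering both arms alike with equal dropout gives 1.00 by symmetry, and excluding deaths alone moved the ratio by only 0.01 to 0.02 at about 7 % mortality, against the PHF. However, adherence is meaningful only where there is a PHF, and Table 1 limits subject compliance to PHF subjects, so one-sided selection is a possible implementation. The Discussion also foresees withdrawal by subjects disappointed with usual care, which sits poorly with the non-differential dropout in the sample size.
- **Detail left to a fuller plan.** How adherence is defined could properly be set there, and its absence here is not the point. The point is that the article does fix conditioning on completion, adherence and duration of use.
- **The remedy.** A complier-average effect is not a simple substitute for a recurrent-event hazard ratio. It needs a binary definition of a complier, and it assumes that allocation acts only through PHF use. The Discussion makes that doubtful by allowing that PHF patients may receive better health attention generally. This stands, so that estimate is offered as an option only.

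**Conclusion.** The concern holds for these two exploratory analyses and no further. On each reading of the text they condition on a variable that death, an endpoint component, helps to determine. The two sections also describe different analyses under the same names. About 19 of 264 subjects per arm are affected at the protocol's 7.25 % mortality, and more if mortality is higher.

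The distortion depends on implementation. Under no effect it is about zero if both arms are filtered alike and dropout does not differ. It reaches a ratio of about 0.93 at 7.25 % mortality if only the PHF arm is filtered, and 0.84 to 0.89 (or the reciprocal, 1.12 to 1.19) if health-related dropout differs by arm as assumed above. These sizes rest on assumptions that are not in the document, and neither direction nor size can be fixed from it. This is a modest correction to exploratory work.

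**What to change.** - Reconcile Methods: statistical analysis plan with Other analyses (exploratory), so that each analysis has one definition.
- In the completers analysis, count death before 48 months as completed follow-up and keep all of that subject's events. In the illustration this removes most of the distortion (0.93 becomes about 1.02).
- Do not enter completion as a covariate.
- In the as-treated analysis, treat PHF use as time-varying. This removes the immortal time, but users remain self-selected.
- Alternatively, replace the as-treated analysis with an estimate that keeps all randomized subjects. One example is a complier-average effect with randomized arm as the instrument, on the event rate or the proportion with any event.

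The cost is revised wording and some extra analysis work. PHF-use data are already collected at each retrieval, and deaths and hospitalizations are captured after withdrawal, so no new data collection is needed. The complier-average option gives a wider interval, needs a binary definition of a complier, and rests on an exclusion restriction that must be stated as an assumption.

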#### Additional analyses

9.Health service utilization and health-care costs;10.Medication errors, duplicative investigations;11.Clinical workflow;12.Management plans uptake and documentation;13.Health literacy;14.Information technology and computer expertise and15.Adverse events.

